### Patient allocation and randomization

Patients are randomized to one of three conditions following a predetermined and computer-generated randomization schedule, pre-stratified by degree of pain catastrophizing (PCS) [28] and disability (PDI) [29]. The median scores of the pain catastrophizing and disability data from a previous study are used as cutoffs. Within each stratum, a randomized block design with a block size of nine is used to ensure equal distribution of important patient characteristics. The randomization procedure is performed by a blinded research assistant who prepares sequentially numbered, sealed, opaque envelops. As is common in psychological treatments, it was not feasible to blind patients or therapists to treatment condition.

### Intervention

We translated and adapted the protocol of [name] and [name] [7] for implementing EXP in a German outpatient setting. The intervention is delivered by two PhD students who are clinical psychologists and who received two different sessions of training from [name] and [name]. In addition, each session is supervised afterwards by experienced psychologists. The control condition is a cognitive behavioral treatment for pain patients containing basic elements for the management of chronic pain that are standard in our outpatient clinic. The treatment includes graded activity, relaxation (progressive muscle relaxation) and cognitive interventions such as cognitive restructuring (Table 1). Both interventions are offered in a structured, individual setting with weekly appointments of 50 minutes.

**Table 1 T1:** Overview treatment sessions

**Session**	**EXP_long**	**EXP_short**	**CBT_P**
1	Anamnesis	Anamnesis	Anamnesis
2	Psycho-educational part I	Psycho-educational part I	Psycho-educational part I
3	Psycho-educational part II:	Psycho-educational part II:	Goal setting
	Fear-avoidance model	Fear-avoidance model	
4	Fear hierarchy	Fear hierarchy	Behavior analysis
5	Exposure 1	Exposure 1	Graded Activity I
6	Exposure 2	Exposure 2	Graded Activity II
7	Exposure 3	Exposure 3	Health Behavior
8	Exposure 4	Exposure 4	Progressive Relaxation I
9	Exposure 5	Exposure 5	Progressive Relaxation II
10	Exposure 6	Completion	*Cognitive Intervention I:* Attention Shifting
11	Exposure 7		*Cognitive Intervention II:* Identification of automatic thoughts and core beliefs about pain
12	Exposure 8		*Cognitive Intervention III:* Restructuring of dysfunctional thoughts and beliefs
13	Exposure 9		Individual Session I
14	Exposure 10		Individual Session II
15	Completion		Completion

CBT-P, Cognitive behavioral treatment for chronic pain problems*;* EXP*,* Exposure treatment.

Treatment sessions are video-recorded and a random selection of videos is evaluated for treatment fidelity. Two blinded raters independently assess protocol adherence, treatment contamination and whether the treatments can be differentiated from each other using the method of assessing treatment delivery in clinical trials (MATD) [30]. In advance, treatment elements of both treatments were identified and listed in a randomized order for the ratings.

#### Common features

Both treatments aim to restore functioning and to decrease pain-related disability. The first two sessions of all treatment conditions are identical. At the intake, participants receive printed material, including background information and worksheets. The first appointment serves as an anamnesis interview which is followed by an educational session. During the educational session, general information about pain, factors related to the maintenance of pain, and physical and physiological changes associated with chronic pain are discussed. Finally, all patients are encouraged to develop feasible treatment goals with respect to activities in which they would like to re-engage.

#### EXP - unique features

Graded *in vivo* exposure (Table 1) aims to reduce pain-related disability via overcoming fear of pain/movements. The program offers two versions of exposure: a long form including 15 sessions (10 exposures) and a short form including 10 meetings (5 exposure sessions). After the first two sessions, the patient is encouraged to develop an individualized fear-avoidance model including pain, pain cognitions and avoidance. This circular model serves as a basis for transferring and explaining the therapeutic rationale. During session four, a fear hierarchy is established using the Photo Series of Daily Activities [31]. The patient makes harm ratings of 100 pictures showing daily activities. If the patient has understood the therapeutic rationale and is willing to do exposure he will be gradually confront feared stimuli, which are movements related to pain or potential injuries of the back. Patients are encouraged to engage in these feared activities as much as possible until anxiety levels have decreased. Behavioral experiments are integrated to challenge catastrophic beliefs about the feared consequences of pain or specific movements. This intervention is intended to produce cognitive and behavioral changes and offers the patient the opportunity to regain trust in his or her body. The process of overcoming fear and learning that feared consequences are unlikely to occur is believed to be the main mechanism of treatment.

#### CBT-P unique features

The primary goal of the CBT approach is the same as that of the exposure treatment, that is, to increase functional capacity. However, the method used to achieve this goal is different. CBT-P encourages patients to develop an adaptive style of coping by maintaining a problem-solving orientation. Patients are provided with different strategies to cope with pain. Initially, patients learn to increase activity by dividing the activities they want to perform in smaller steps to avoid phases of excessive demands followed by long terms of recovery. After this first phase, patients learn to practice progressive relaxation. During the third module, maladaptive pain-related cognitions are identified and discussed. Patients are taught to recognize the links between thoughts, feelings and behavior and to challenge negative appraisals as one strategy for interrupting pain-maintaining circuits. The last two sessions are individualized based on topics relevant to the patient (for example, work-related problems). These topics are discussed with a focus on problem-solving.

An additional table file gives an overview of the treatment sessions in more detail (see Additional file 1, Table 1).

### Outcomes

For outcomes related to pain, we followed the recommendations from the Initiative on Methods, Measurements, and Pain Assessment in Clinical trials (IMMPACT, [32]).

#### Primary outcome measures

Pain-related disability is measured using the Pain Disability Index (PDI) [29,33] and the Quebec Back Pain Disability Scale (QBPDS) [25].

Pain intensity is assessed four times a day using a two-week pain diary comprising an 11-point numeric rating scale (NRS) (0 = no pain, 10 = pain at its worst) and an 11-point scale from the German Pain Questionnaire (Deutscher Schmerzfragebogen,DSF) assess average pain intensity during the past four weeks [34].

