#### Research questions

1) Is EXP more effective (at post-treatment and at six-month follow-up) at reducing pain-related disability and pain intensity (primary outcomes) as well as other symptoms compared to CBT-P in patients with fear-avoidance beliefs?

2) Are there any differences in treatment effects between the short (10 sessions) and the long (15 sessions) versions of exposure at post-treatment and at six-month follow-up?

3) What is the cost-effectiveness of EXP as compared to CBT-P?

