### Sample size calculation

To identify the target number of participants we used the G-Power Analysis software program (University of Düsseldorf, Germany http://www.psycho.uni-duesseldorf.de/abteilungen/aap/gpower3.) [27]. Based on the effects of previous RCTs, we expected a small effect group x time (repeated measures) of 0.2 for the comparison of three groups (assuming an alpha level = 0.05, two-tailed, β = 0.95, correlation between measurements = 0.5). Results of the power analysis indicated a required sample size of 36 participants per group, for a total of 108. The data will be analyzed with the intent-to-treat (ITT) approach using the last value carried forward and including all patients who intended to participate, regardless of whether they dropped out or not.

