### Data analysis

The latest version of The Statistical Package for Social Science (IBM SPSS Statistics) version 19is used for data analyses. Intention-to-treat analyses (ITT) used to account for deviations from random allocation and missing data. A repeated measures design will be used with primary and secondary measures as dependent variables, group as the between-subjects factor, and time of measurement as the within-subjects factor.

Possible confounding variables (for example, duration of complaints) will be considered and included as covariates according to the results of correlation analyses. Effect sizes (Cohen´s d) will be calculated to determine the magnitude of the mean differences between groups on the outcome variables. According to Cohen´s guidelines, an effect size of .2 indicates a small effect, .5 a medium effect and .8 a large effect [52]. We consider a 30% reduction on the NRS to indicate clinically important change on the core outcome measure of pain intensity [53]. The economic evaluation consisted of a cost-utility analysis and a cost-effectiveness analysis. For both analyses, the incremental cost-effectiveness ratio (ICER) was calculated as (C1-C0)/(E1-E0) where C is the cost and E is the effect and the experimental and comparator conditions are indexed with the 1, 0 subscripts.

The incremental cost-utility ratio will focus on the net costs per quality adjusted life years (QALY) gained. The cost-effectiveness ratio focuses on the net costs per reliable and clinically improved case of disability/pain. Probit analysis will be used for dose–response effects. This approach based on probability theory and includes determining the observed rates and resulting probability of a response for a particular treatment.

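### Four unranked primary instruments, and a three-group group-by-time test that does not by itself answer whether exposure beats CBT-P

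*Protocol article*

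**What the plan says.** Primary outcome measures lists two instruments in each of two domains. For disability: "Pain-related disability is measured using the Pain Disability Index (PDI) [29,33] and the Quebec Back Pain Disability Scale (QBPDS) [25". For pain intensity there is a two-week diary with a numeric rating scale (NRS), and "an 11-point scale from the German Pain Questionnaire" (DSF) covering average pain over the past four weeks. No order among the four is given.

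Research question 1 reads: "Is EXP more effective (at post-treatment and at six-month follow-up) at reducing pain-related disability and pain intensity (primary outcomes". Question 2 is separate and compares the short with the long version of exposure, at the same two time points.

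The sample size paragraph states: "we expected a small effect group x time (repeated measures) of 0.2 for the comparison of three groups". Its assumptions are "assuming an alpha level = 0.05, two-tailed, β = 0.95, correlation between measurements = 0.5", and its result is a "required sample size of 36 participants per group, for a total of 108".

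Data analysis says: "A repeated measures design will be used with primary and secondary measures as dependent variables", with group as the between-subjects and time as the within-subjects factor. It writes no contrast of EXP with CBT-P and states no significance level. It adds Cohen's d for differences between groups and a probit analysis for dose-response.

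**The concern.** Two problems meet here.

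- **Which result decides.** There are four primary instruments, but the trial is sized for a single test at a single alpha. If the plan is followed as written, four models are fitted and any one significant result could be reported as the primary finding.
- **What the test shows.** A three-group interaction asks whether the three arms change differently over time in any way. Question 1 asks whether exposure does better than CBT-P. A significant interaction can come from the two exposure arms differing from each other, which belongs to question 2. No contrast is written that separates the two.

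At stake is whether a reader can tell, before results are known, what would count as an answer to question 1 and how likely that answer is to arise by chance.

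**Working it through.** **The plan's own figure.** Inputs from the sample size paragraph: effect 0.2 (read as Cohen's f), alpha 0.05, correlation 0.5, three groups. The printed β of 0.95 is read as power. The number of measurements m is not stated; m = 2 is assumed. For the within-between interaction:

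- λ = f²·N·m/(1−ρ), with df₁ = (3−1)(m−1) and df₂ = (N−3)(m−1).
- At N = 108: λ = 0.04 × 108 × 2 / 0.5 = 17.28, with df 2 and 105. Power is 0.965.
- The smallest N for 0.95 is 100, or 102 in equal groups. Rounding 100 up to whole blocks of nine gives 108 (the rounding is an assumption).

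So the stated size is reproduced, within two patients per group, for **one** three-group test at 0.05. With m = 3, 81 patients would suffice.

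**Does that test answer question 1?** Its power depends on f, not on which arms differ. Take m = 2, so that the change score has SD √(2(1−0.5)) = 1. Suppose pooled EXP truly equals CBT-P and the two EXP arms lie at +a and −a around it. Then 36 × 2a² = 17.28, so a = 0.49 and long differs from short by 0.98 SD of change. In simulation the three-group test is significant in about 96% of trials, and a pooled EXP v CBT-P contrast in about 5%. The example is extreme, but it shows that the powered test can succeed almost always when pooled exposure is no better than CBT-P.

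**False primary results.** For k independent tests at 0.05 the chance of at least one is 1 − 0.95ᵏ:

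- k = 4: 18.5%
- k = 8: 33.7%
- k = 16: 56.0%
- k = 24: 70.8%

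The four instruments will be correlated, so the null case was also simulated: 36 per arm, baseline plus two later time points, correlation 0.5 between times, 40,000 trials per setting. The instrument correlations are assumptions; the article gives none.

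| Tests, each at 0.05 | r = 0.3 | r = 0.5 | r = 0.7 |
|---|---|---|---|
| Named analysis: one interaction per instrument (4) | 17.7% | 15.7% | 13.7% |
| Pooled EXP v CBT-P, per instrument and time (8) | 29.8% | 26.8% | 22.7% |
| Of these, at least one favouring EXP | 15.3% | 13.5% | 11.2% |
| The 8 plus long v short (16) | 50.6% | 46.6% | 39.9% |
| All three pairs (24) | 58.6% | 53.7% | 46.3% |

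Only the first row is the analysis that the article names. The interaction already covers all arms and time points, so these do not multiply the count.

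**The case against.** A reader might infer that four instruments, two time points and three arms are all tested at 0.05, so that a primary success arises by chance about half the time. The document does not support this, for three reasons:

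- The named analysis is four tests. Reaching about half takes 16 separate unadjusted contrasts, which the article does not specify. Eight of those would be direct EXP v CBT-P comparisons, so the figure cannot be combined with the complaint that question 1 goes untested. The other eight are long v short, which is question 2. Nor is half a ceiling: all pairs give more.
- The level of 0.05 appears only in the sample size paragraph. That each instrument would be tested at 0.05 is an inference, though a natural one.
- The two-sided figures include false results favouring CBT-P. A false result for EXP on question 1 is about half as likely.

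It is also fair to say that a multiplicity rule may stand in an analysis plan or full protocol not shown, so its absence alone is no error. Some text helps as well. Objectives speaks of a short and a long version of EXP, so EXP most naturally means both arms. Dose-response has its own probit analysis. Data analysis describes pain intensity as the core outcome when it sets a 30% threshold on the NRS, which hints at priority among the pain measures.

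These points reduce the size of the problem. They do not remove it. The article itself makes the choice of primary measures and names four, and the test that it powers and names does not match question 1. Cohen's d describes group differences but is not a test, and the NRS remark ranks nothing on the disability side.

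**Conclusion.** The concern holds in this form: four unranked primary instruments, a sample size for one test, and a three-group interaction that does not by itself answer question 1.

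- If each instrument is tested at 0.05, the named analysis gives about 14 to 18% for at least one false primary result (18.5% if independent), roughly three times nominal.
- If question 1 is instead tested as pooled EXP v CBT-P per instrument and time point without adjustment, the figure is about 23 to 30% two-sided, or about 11 to 15% favouring EXP.
- About 40 to 51% is reached only by also counting long v short.

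These figures rest on an assumed instrument correlation of 0.3 to 0.7 and a correlation of 0.5 between time points. The mismatch between test and question needs no such assumption: it follows from the text. This should be corrected, but it does not put the design itself in doubt.

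**What to change.** Before analysis, state in the protocol or analysis plan:

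1. The confirmatory contrast for question 1 is both EXP arms pooled against CBT-P, estimated within the repeated-measures model.
2. One disability measure, one pain measure and one time point are primary. Which ones is the sponsor's choice, made without sight of outcomes by arm.
3. The two measures are tested by Holm at an overall two-sided 0.05.
4. Only if both are rejected, EXP_long v EXP_short is tested next in fixed sequence, on the same two measures and again by Holm.
5. The remaining instruments and the other time point are secondary. The three-group interaction is descriptive.

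**Cost.** This is a change of wording. Trial status reports 71 of 108 randomized by May 2013 and data expected in 2014, so at publication there was time to make it. There is some loss of sensitivity. For 72 v 36 at 80% power the detectable d is (z + 0.842) × √(1/72 + 1/36), where the root is 0.204:

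- alpha 0.05: 2.802 × 0.204 = 0.57
- first Holm step, 0.025: (2.241 + 0.842) × 0.204 = 0.63

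With baseline adjustment at an assumed correlation of 0.5, both are multiplied by √(1 − 0.25) = 0.866, giving 0.50 and 0.55. Either way the rise is about 10%. Pooling can also hide a benefit confined to one exposure arm. If the sponsor means EXP_long alone, the plan should say so instead.

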#### Secondary outcomes

Fear of movement/pain anxiety is measured using the Tampa Scale of Kinesiophobia (TSK) [23,35] and The Pain Anxiety Symptom Scale (PASS) [36,37]

Pain catastrophizing is assessed using the Pain Catastrophizing Scale (PCS) [28,38].

Emotional distress is measured using the Hospital Anxiety and Depression Scale (HADS) [39,40].

Quality of Life is measured using the EuroQol Questionnaire (EQ-5D) [41,42].

Pain vigilance is measured using the Pain Vigilance and Attention Questionnaire (PVAQ) [43,44].

Physical activity is assessed using the International Physical Activity Questionnaire (IPAQ) [45].

Global perceived effect of treatment is rated on a 7-point scale (1 = completely recovered, 7 = worse than ever) to assess subjective perceptions of recovery.

All instruments have been widely used and demonstrated reliability and validity in the chronic pain population.

#### Tertiary outcomes

The tertiary outcomes include: the Pain Solutions Questionnaire (PASOL) [46], the Psychological Inflexibility in Pain Scale (PIPS) [47], scales assessing coping with pain (Fragebogen zur Erfassung der Schmerzverarbeitung, FESV) [48] and the Pain Self Efficacy Questionnaire (FESS) [49].

#### Additional variables

Several additional variables are assessed in order to examine potential mechanisms of treatment and to assess feasibility and treatment fidelity.

Satisfaction with treatment as a measure of feasibility is evaluated with 10 items on an 11-point scale (0 = strongly disagree, 10 = absolutely agree). In addition, the therapists assessed feasibility in a qualitative manner including a standardized dropout evaluation and assessment of adverse effects.

All therapy sessions are documented within a table, including notes and information about the participants based on evaluations of the therapists or supervision. The therapist also notes when he or she thinks that the assigned treatment approach is not fully adequate for this patient. Furthermore, a standardized dropout evaluation was developed. If a patient breaks off treatment, an independent research assistant asks the participant standardized questions about the reasons for refusing the treatment and possible adverse effects of treatment.

Sessions will be evaluated for treatment fidelity by a research assistant blind to treatment conditions. The fidelity evaluation is based on the approach of Leeuw and colleagues who developed a method of assessing treatment delivery in clinical trials (MATD) [30].

Treatment expectancy and rationale credibility is measured with the credibility and expectancy questionnaire (CEQ) [50].

The therapeutic alliance is measured on an 11-point scale including 13 items (0 = strongly disagree, 10 = absolutely agree).

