**Methods:**

A total of 108 chronic low back pain patients are randomly assigned to one out of three conditions (A: exposure_long (15 sessions), B: exposure_short (10 sessions) or C: control condition cognitive behavioral therapy (15 sessions)). The inclusion criteria are: back pain ≥3 months and a sufficient level of fear-avoidance. An effect evaluation, a process evaluation and an economic evaluation are conducted. Primary outcomes are pain-related disability and pain intensity. Secondary outcomes are: emotional distress, fear avoidance, catastrophizing and costs. Data are collected at baseline, upon completion of the intervention, after 10 sessions, and at six months following completion of treatment. Besides the comparison of exposure *in vivo* and cognitive behavioral therapy (CBT), we additionally compare a short and a long version of exposure to analyze dose response effects.

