### Data collection

Data are collected at baseline (T0), after 10 sessions (T1, completion of EXP short), upon completion of the intervention (T2), and six months following completion of treatment (T3). Thus, participants in the short version of EXP complete only three assessments. Questionnaires are completed at home via the internet. This procedure reduces missing data and helps to keep study therapists blind to outcome data. Supplemental evaluations are carried out weekly, including process variables. If patients do not have internet access the assessment are provided on a computer in our outpatient clinic. Video recordings are carried out during each session to gather objective data for later analysis of treatment fidelity.

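### Adverse effects are sought by standardised questions only from patients who break off treatment, so they are probably under-counted in completers and any comparison of arms on them would be at risk of bias

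*Protocol article*

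**What the plan says.** The Additional variables section describes two routes for finding adverse effects.

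- **All patients:** "the therapists assessed feasibility in a qualitative manner including a standardized dropout evaluation and assessment of adverse effects". In addition, "All therapy sessions are documented within a table, including notes and information about the participants based on evaluations of the therapists or supervision".
- **Patients who stop early:** in that event, "an independent research assistant asks the participant standardized questions about the reasons for refusing the treatment and possible adverse effects of treatment".

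Patient allocation and randomization states that "it was not feasible to blind patients or therapists to treatment condition", so the therapists' assessment is made with knowledge of the arm. The abstract and Table 1 give 15 sessions for long exposure, 10 for short exposure and 15 for CBT-P. Data collection says of the outcome measures: "Questionnaires are completed at home via the internet". No measure listed under Outcomes, Process evaluation, Economic evaluation or Data collection asks completers about adverse effects.

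**The concern.** The instrument, the assessor and the assessor's independence all change when a patient breaks off treatment. That event follows randomisation and may itself be caused by the treatment. A count of adverse effects drawn from both routes would mix how often they occur with how hard they were looked for.

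This matters because exposure asks patients to perform movements that they fear will injure their back. The article calls the approach new to the German health care system and intends to establish its feasibility, and it places adverse effects within that feasibility assessment. Completers received the full treatment, yet the independent standardised questions are not put to them. Both described routes are also tied to the treatment period or to leaving it. Neither asks completers about adverse effects during the six months up to T3.

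**Working it through.** The article gives no adverse-effect rate, dropout rate or harms count, so there is no stated figure to reproduce. The check is first a reading of the text, then an illustration on assumed values.

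**Text.**

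| | Patient breaks off | Patient completes |
|---|---|---|
| Therapist assessment and session notes | yes, up to stopping | yes, over 10 or 15 sessions |
| Standardised adverse-effect questions | yes | none described |
| Independent assessor | yes | none described |
| Scales that can show worsening | yes, where completed | yes |

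**Illustration 1: dependence on dropout.** Let p be the true risk, d the dropout proportion, s_d the chance that an adverse effect is found in a dropout, and s_c the same chance in a completer.

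Observed risk = p × [d × s_d + (1 − d) × s_c]

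Assume p = 20% in both arms and s_d = 0.9, with s_c from 0.3 to 0.9. The only input from the document is 36 patients per arm (Sample size calculation).

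| s_c | Dropout, arm 1 v arm 2 | Observed risk | Ratio | Difference in patients per 36 |
|---|---|---|---|---|
| 0.3 | 10% v 10% | 7.2% v 7.2% | 1.00 | 0 |
| 0.3 | 10% v 30% | 7.2% v 9.6% | 1.33 | 0.9 |
| 0.5 | 10% v 30% | 10.8% v 12.4% | 1.15 | 0.6 |
| 0.7 | 10% v 30% | 14.4% v 15.2% | 1.06 | 0.3 |
| 0.9 | 10% v 30% | 18.0% v 18.0% | 1.00 | 0 |

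First row: 0.20 × (0.10 × 0.9 + 0.90 × 0.3) = 0.072. The last row is uniform questioning.

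- *Under-count.* Uniform questioning finds 0.20 × 0.9 = 18.0%, or 6.5 of 36 patients. At 10% dropout the two-route scheme finds 2.6 patients (s_c = 0.3) to 5.2 (s_c = 0.7). It misses 60% to 20% of the detectable cases, about 3.9 to 1.3 patients per arm.
- *Between arms.* The spurious difference equals p × (d2 − d1) × (s_d − s_c). For the second row this is 0.20 × 0.20 × 0.6 = 2.4 percentage points. It vanishes if dropout is equal or if both routes detect equally well, and it changes sign if s_d is below s_c.

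**Illustration 2: dependence on contact.** If each session has a chance q of producing an adverse-effect entry, independently, the chance of at least one entry over n sessions is 1 − (1 − q)^n.

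| q (assumed) | 10 sessions | 15 sessions |
|---|---|---|
| 3% | 26% | 37% |
| 5% | 40% | 54% |
| 10% | 65% | 79% |

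This gap needs no difference in dropout. It affects short exposure against the other two arms, because long exposure and CBT-P both have 15 planned sessions. Part of such a gap could be real, from longer treatment, and session notes alone cannot separate that from more occasions to record.

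**The case against.** The strongest reply is that the plan makes no comparison that this would spoil. Adverse effects do not appear in the Research questions, the outcome lists or Data analysis, and no rate or between-arm test is announced. That stands: the risk attaches to any harms statement later drawn from these data, not to a planned test.

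Second, completers are not without any signal. Sessions are supervised and video-recorded, and all arms have global perceived effect, HADS, health-care use and weekly PDI, QBPDS and pain ratings. These would show deterioration by the same means in each arm. That stands in part. They record status and do not elicit adverse effects, and the stated use of the videos is treatment fidelity. Data collection also says that online completion helps keep therapists blind to outcome data, so the people assessing completers' adverse effects are not meant to see the scales.

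Third, in the sentence on therapists, the word for standardised could be read as covering their adverse-effect assessment too. The same sentence calls their work qualitative, and the only standardised questions described are those for patients who stop. An article may leave the form of an assessment to the full protocol, but here the article itself states which patients receive those questions.

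Fourth, a reader might infer that the arm losing more patients will look more harmful. The document does not support that. Dropouts attend fewer sessions, so therapists have fewer occasions to note an effect, and the exit interview may only offset this. Both the direction and the size depend on unknown detection and dropout rates.

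**Conclusion.** The point holds as a weakness in a stated design choice. How adverse effects are found depends on whether the patient stays in treatment, and completers are covered by unblinded, qualitative recording over unequal numbers of sessions. Under-counting in completers is likely, on the assumption that qualitative notes find less than direct standardised questions. Bias between arms is a risk that requires dropout, therapist recording or contact to differ. Of these, the document shows only the difference in contact, 10 v 15 sessions.

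The size is unknown. On the assumed figures the under-count (1.3 to 3.9 patients per arm at 10% dropout) is larger than the spurious difference from unequal dropout (0.3 to 0.9 patients at 10% v 30%). A reader might conclude that harms are demonstrably under-counted and that the arms cannot be compared. The document does not show that much, because it contains no rates and plans no formal harms comparison. The primary outcomes are unaffected. What is weakened is the adverse-effect part of the feasibility conclusion.

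**What to change.** Add one short set of standardised adverse-effect questions to the existing online questionnaires for all randomised patients, including those who break off treatment. Ask it twice in every arm: at the end of the assigned treatment (T1 for short exposure, T2 for long exposure and CBT-P) and at six-month follow-up (T3). Asking at T1, T2 and T3 would not be even, because short-exposure patients complete only three assessments including baseline and would be asked once less often than the others.

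State that any comparison of harms between arms rests on this common instrument alone. Keep the dropout interview and the therapists' notes as supplementary description.

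The cost is a minor amendment and slightly more patient burden. The recall period to the end of treatment is longer in the 15-session arms. By May 2013, 71 of 108 patients had been randomised, leaving 108 − 71 = 37 who could be covered in full from the start. Patients already past treatment would answer retrospectively at T3, and those past follow-up would be missing. The report should say how many fall into each group, by arm.
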